#### Other exploratory outcomes and covariates

For anthropometric and body composition evaluation, the weight and height will be measured by means of a digital scale with a stadiometer (Welmy model W300; São Paulo, Brazil) with a capacity of 300 kg, an accuracy of 50 g and a stadiometer with limit of 2 m. Body mass index will be calculated by dividing the body weight by the height squared (kg/m^2^). Trunk muscle mass and the upper and lower limbs will be evaluated using the InBody R20 electrical impedance scale (Biospace Co. Ltd., Korea), which uses a low-amplitude, high-frequency electric current to calculate the percentages and totals of water and fat in the body, and the metabolic rate.

Cardiopulmonary evaluation will be measured by the peripheral oxygen saturation, heart rate, systolic and diastolic blood pressures and the respiratory rate using a DIXTAL 2023 multiparameter monitor (Manaus, Brazil).

### Sample size calculation

The sample size was calculated using the G*Power Program (Version 3.1.9.2, University of Kiel, Germany) and the variable VO_2peak_ (in liters per minute) was adopted as the primary outcome measure. According to a previous study involving individuals with poststroke hemiparesis who performed cycling training [48], standard deviations observed in the experimental and control groups were 0.16 and 0.13, respectively. The sample size was calculated from these data to detect a difference in VO_2peak_ between the groups after intervention of 0.24 l/min (α = 5% and power = 80%), using a two-sample *t* test for mean difference. The sample required was eight patients; considering a follow-up loss of 20%, 10 individuals will be allocated into each intervention group: 10 individuals in the experimental lower limb group (cardiorespiratory training of the lower limbs plus PNF), 10 individuals in the control lower limb group (cardiorespiratory training of the lower limbs plus breathing), 10 individuals in the experimental upper limb group (cardiorespiratory training of the upper limbs plus PNF) and 10 individuals in the control upper limb group (cardiorespiratory training of the upper limbs plus breathing).

### Statistical analyses

A descriptive analysis of the data will be initially performed. Frequency distribution will be obtained for the categorical variables, and central tendency and dispersion measures will be obtained for the numerical variables. The Kolmogorov-Smirnov/Shapiro-Wilk test and the Levene test will be used to evaluate the normality of the variables and the homogeneity of the sample, respectively.

All tests will be applied assuming a 95% confidence level, considering a significant *P* value <0.05. An intention-to-treat analysis will be performed in case of patient withdrawal or interruption of training, using the last observation carried forward. Two-way repeated-measures analysis of variance to determine the interaction intervention by time (pretraining, post-training and 30 days of follow up) for the outcome variables will be conducted for the experimental and control lower limb interventions and the experimental and control upper limb interventions separately. Paired *t* tests will be used to compare clinical outcomes between preintervention and post-training for experimental and control groups. Independent *t* tests will be also used to separately compare upper limb experimental and control groups and lower limb experimental and control groups post-training.

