### Intervention and control

Twenty sessions will be performed with breathing exercises (spontaneous breathing or using PNF patterns), followed by aerobic exercises for lower or upper limbs, and ending with repetition of the respiratory exercises.

The session will begin with the breathing patterns, with each pattern/exercise being performed 10 times. The therapist will position the hands to perform the maneuvers (Fig. 1). In the control group, the patients will put their hands in the same locations used by the therapist during the PNF (Fig. 2).

The cycling will be performed for 30 min per session. Cycling training will be performed without load with a minimum start speed of 50 rpm following the recommendation of the American College of Sports Medicine for patients with stroke [28]. Participants will be encouraged to increase the number of revolutions per minute throughout the study. Thus, participants will perform the cycling at 50 rpm at the beginning; however, there will not be a minimum number of revolutions per minute to reach by the end of the treatment. The patients will be instructed to develop and maintain their highest speed during the exercise, but they may pause if they feel fatigued or need to slow down.

To perform cardiorespiratory training, individuals must be able to remain safe and stable during cycling, with the paretic limb positioned and tied to the pedal. The volunteers will be monitored every 5 min during the 30 min of exercise on the cycle ergometer to check blood pressure, peripheral oxygen saturation and heart rate. The participants will also be asked about their perception of respiratory effort and fatigue in the limbs at the beginning and end of the activity using the original [29] and modified Borg Scale, respectively.

Three evaluations will be carried out at different times: pretraining, post-training and at 30-day follow-up.

The volunteer can be allocated to one of the following protocols:

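### Last observation carried forward enters baseline VO2peak as the result for participants with no post-training assessment; this dilutes the PNF contrast under equal loss, can bias it either way under unequal loss, and does not match the sample size reasoning

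*Protocol article*

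**What the plan says.** Under Statistical analyses, the protocol article sets one rule for missing outcomes: "An intention-to-treat analysis will be performed in case of patient withdrawal or interruption of training, using the last observation carried forward". The visit schedule, under Intervention and control, is: "Three evaluations will be carried out at different times: pretraining, post-training and at 30-day follow-up". Nothing is measured between the first two.

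Under Sample size calculation, the trial is sized on VO2peak with a two-sample t test: "standard deviations observed in the experimental and control groups were 0.16 and 0.13, respectively", and the target is a difference "between the groups after intervention of 0.24 l/min (α = 5% and power = 80%), using a two-sample" t test. Loss is handled by inflation: "The sample required was eight patients; considering a follow-up loss of 20%, 10 individuals will be allocated into each intervention group".

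The planned tests are an intervention-by-time interaction from repeated-measures analysis of variance, paired t tests, and independent t "tests will be also used to separately compare upper limb experimental and control groups and lower limb experimental and control groups post-training".

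Under Participant withdrawal, participants who miss a set number of sessions are excluded from the study. So losses during training are foreseen.

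**The concern.** With three visits, carrying forward does two different things. A participant who never has the post-training assessment has only baseline to carry, so the analysis records no change. A participant lost after post-training has that value copied to 30 days, so the analysis records full retention of benefit. The article supports neither assumption, and filled values are then treated as if they had been observed.

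The two sections also disagree on what happens to lost participants. Going from 8 to 10 makes sense if two per group drop out and eight complete cases carry the full 0.24 l/min. The analysis section keeps all ten, and some of them may carry zero change.

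Both arms receive the same kind of cycling, and the Background calls aerobic training effective, so controls may improve too. Recording zero change then removes real gain from whichever arm loses more participants, and the PNF contrast moves with it. With ten per arm, a few filled values can move the result materially.

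**Working it through.** **Inputs from the article.** SDs 0.16 and 0.13; difference 0.24 l/min; alpha 5%; power 80%; 8 per group, 10 after 20% loss; three visits.

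**Assumed, because the article does not give them.** Two-sided test; baseline-to-post correlation 0.7 (0.5 and 0.8 also tried); training gain in controls of 0, 0.12 or 0.24 l/min; timing and split of losses as stated in each case.

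**Step 1: reproduce the plan's figure.** Common SD = √((0.16² + 0.13²)/2) = 0.1458, so the standardised difference is 0.24/0.1458 = 1.65. The two-sided t test has 80.7% power at 7 per group and 86.4% at 8. With SD 0.16 in both arms, 8 per group gives 79.7%. The stated 8 is reasonable, and 8/0.8 = 10 as stated.

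**Step 2: expected difference after carrying forward.** Let g be the control gain, δ the PNF effect, and qE and qC the fractions with no post-training assessment in the PNF and control arms. Then

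expected difference = (1 − qE)(g + δ) − (1 − qC)g.

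- Equal loss of 20%, δ = 0.24: 0.8 × 0.24 = 0.192, whatever g is.
- No PNF effect, g = 0.24, loss 30% PNF and 10% control: (0.7 − 0.9) × 0.24 = −0.048, a fifth of the design difference, against PNF.
- No PNF effect, g = 0.24, loss 0 PNF and 4 of 10 control: (1 − 0.6) × 0.24 = +0.096, in favour of PNF.
- δ = 0.24, g = 0.10, loss 4 of 10 PNF and 0 control: 0.6 × 0.34 − 0.10 = 0.104. With the loss reversed: 0.34 − 0.6 × 0.10 = 0.280.

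**Step 3: power under equal loss.** Filled values also add spread, because an arm becomes a mixture of changed and unchanged participants. With 20% loss and no control gain, the SD becomes √((0.16² + 0.8 × 0.2 × 0.24² + 0.13²)/2) = 0.161. A difference of 0.192 with 10 per arm then has 71.4% power. Dilution alone, with the SD left at 0.1458, gives 79.5%.

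Simulation, with losses before post-training and SD 0.1458:

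| Lost per arm | Control gain | Difference | Post-training t test | Pre-to-post change, correlation 0.7 (0.5 to 0.8) |
|---|---|---|---|---|
| 1 of 10 | 0 | 0.216 | 85% | 98% (89% to over 99%) |
| 2 of 10 | 0 | 0.192 | 72 to 73% | 96% (83% to 99%) |
| 2 of 10 | 0.12 | 0.192 | 61 to 62% | 87% (71% to 96%) |
| 2 of 10 | 0.24 | 0.192 | 45% | 63% (50% to 74%) |
| 3 of 10 | 0 | 0.168 | 57% | 91% (about 74% to 98%) |

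The benchmark for the post-training t test is 86% with 8 completers per arm and 94% with 10. The correlation hardly affects this test. The change comparison stands in for the planned interaction test.

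**Step 4: false positives under unequal loss.** With no PNF effect and g = 0.24, the t test rejects in about 5% of runs at 3 versus 1 lost, and in about 19% at 0 versus 4 lost.

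**The case against.** Four points against the concern have weight.

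- **Not every withdrawal is filled with baseline.** A reader might infer that anyone who withdraws is. The article does not support this. Interrupting training is not the same as missing the assessment, and a participant lost after post-training keeps the observed post-training value.
- **The timing of the 20% is not given.** Follow-up elsewhere in the article usually means the 30-day visit. If the loss falls there, the post-training t test is untouched. Putting all of it before post-training is the worst case for equal 20% loss.
- **The t test is the less favourable of the planned tests.** The interaction is named first, and the change comparison holds above 80% in several cases. That rests on the correlation, though: at 0.5, a control gain of 0.12 already takes it to 71%.
- **Zero change may be close to the truth for someone who stops early.** The article does not say what such participants would gain, so the diluted value cannot be called wrong for every individual.

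These points limit the size of the problem but do not remove it. The single stated rule fills the outcome with baseline whenever post-training is missing, and its bias depends on which arm loses more. The lack of a described sensitivity analysis is not held against the article, since a separate analysis plan may contain one.

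**Conclusion.** The concern holds in a conditional form. Participants with no post-training assessment are analysed as unchanged, and those lost later as having kept their full benefit. Equal loss dilutes the contrast by the fraction lost: 20% gives 0.192 instead of 0.24 l/min. Unequal loss, with gains in both arms, shifts it either way: −0.048 or +0.096 l/min in the cases shown, both with an assumed common gain of 0.24. At 3 versus 1 lost the harm is a biased estimate, with rejection still near 5%; at 0 versus 4 rejection reaches about 19%.

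Two stronger readings are tempting. One is that carrying forward always shrinks the effect; more loss among controls can inflate it or create one. The other is that the trial falls short of 80% power as a matter of fact. The post-training t test does so at 2 of 10 lost per arm before post-training (about 73%, or less with control gains), but not at 1 of 10 with no control gain (85%). The article does not fix the timing.

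The mismatch between the sample size reasoning and the analysis rule needs no assumption: one removes lost participants and the other retains them with filled values.

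**What to change.** 1. Make the primary analysis a likelihood-based linear mixed model for repeated measures on all observed visits, within each limb comparison, with participants analysed as randomised and baseline accounted for. State its missing-at-random assumption. A participant with baseline only adds almost nothing to the post-training contrast, so the model does not replace collecting the data.
2. Keep last observation carried forward at most as a labelled sensitivity analysis.
3. Reconcile the exclusion rule under Participant withdrawal with the intention-to-treat statement under Statistical analyses, so that participants who miss sessions still contribute any post-training and 30-day assessments.
4. State under Sample size calculation how lost participants enter the analysis, so that the step from 8 to 10 matches it.

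The cost is revised wording before unblinding; the article reports recruitment as ongoing. No larger sample is needed for this point. The only added effort is inviting participants who stop training to the two remaining assessments.

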A home/community physiotherapy program of aerobic and respiratory exercises that could provide increments in the time of active exercise in this population [2] might be attractive to the individual and their family since such a program could reduce the time of intensive rehabilitation and the costs, and restore independence, with a consequent improvement in quality of life [19]. Aerobic exercise training is well known as an effective approach to improve aerobic fitness [20]. Exercises on a cycle ergometer performed for both the upper and lower limbs allow the patient to perform an activity load with a focus on the range of motion, coordination, muscle strengthening and increased exercise tolerance [20, 21]. These exercises are also well tolerated in patients with stroke [22].

As an alternative strategy to stimulate active breathing associated with stretching of the antero-posterior, cranio-caudal and latero-lateral diameters of the trunk, respiratory exercises following the principles of proprioceptive neuromuscular facilitation (PNF) have gained more interest for the treatment of patients with stroke [23, 24]. This approach imposes great awareness of the performed movement on the individual, a factor that is usually not present and which could be helpful in the rehabilitation of patients with stroke [25]. The use of PNF has been traditionally for rehabilitation to address motor impairments related to musculoskeletal parameters such as strengthening and/or stretching of paretic limbs and motor control/motor learning [26]. However, the effectiveness of this technique on respiratory parameters is still little known. In a recent study, respiratory pattern exercises of PNF performed in patients with stroke showed a decrease in bioelectrical activity of the accessory respiratory muscle, which could be related to muscle relaxation and reduction of spasticity and which thus could improve respiratory function [24]. Therefore, we hypothesized that the association of aerobic exercises and exercises with a focus on the respiratory musculature may be a therapeutic alternative capable of improving several functional negative outcomes after a stroke.

The objective of this protocol is to assess the effects of PNF respiratory exercises associated with cardiorespiratory training on respiratory and trunk characteristics, specifically on the quality of life, gait parameters, VO_2peak_, respiratory muscle strength, and thoracic chest wall volumes in patients poststroke.

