### Participant withdrawal

Patients who miss three consecutive sessions or five intercalated sessions without replacement will be excluded from the study. Also, if the participant reports that they no longer wish to continue they may withdraw from the study at any time.

Participants will be made aware that they are not expected to undergo any other type of physiotherapeutic treatment in order to reduce the risk of interference in the proposed intervention. This requirement will not be enforced in the period between the postintervention evaluation and the follow-up evaluation, but will be recorded if it occurs.

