## Discussion

### Relevance of the study

The purpose of this clinical trial is to evaluate the efficacy of the addition of PNF patterns performed on the trunk to cardiorespiratory training in patients with stroke. Although there are a number of studies, including systematic reviews [1, 20], which clarify the need to increase the frequency of physical exercise in this population or discuss exclusive training for respiratory muscles [49], the union of these therapies is still not well documented in the literature.

The focus of treatment on respiratory muscles through PNF respiratory patterns provides an innovative approach for patients with stroke undergoing cardiorespiratory rehabilitation. In our protocol, stabilization reversal which is characterized by alternating isotonic contractions opposed by resistance to prevent motion, will be used as a specific PNF technique. We will apply these techniques in several positions, both seated and supine. The patterns of PNF associated with respiration will be performed 10 times for both PNF and control groups.

To date, we have found only one study that applied PNF respiratory patterns in patients with stroke; however, this study focused on electromyography activities, and information about the influence of PNF techniques on aerobic capacity, pulmonary function and chest wall distribution is still lacking.

Thus, we believe that our protocol will improve the current literature since the association of PNF therapy and cycle ergometer training could provide a more affordable therapy, and is feasible for use in the early stages and in various therapeutic settings to improve respiratory function.

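### Three tests at P<0.05 bear on the same PNF question and none is named as decisive; the within-arm paired tests cannot answer it and the post-training t test wastes the baseline

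*Protocol article*

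**What the plan says.** The Discussion (Relevance of the study) gives the purpose as to "evaluate the efficacy of the addition of PNF patterns performed on the trunk to cardiorespiratory training in patients with stroke". That is a comparison between arms.

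Statistical analyses lists three inferential procedures, applied separately to the lower-limb and upper-limb pairs:

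1. "Two-way repeated-measures analysis of variance to determine the interaction intervention by time (pretraining, post-training and 30 days of follow up").
2. Paired t tests: "tests will be used to compare clinical outcomes between preintervention and post-training for experimental and control groups".
3. Independent t tests: "tests will be also used to separately compare upper limb experimental and control groups and lower limb experimental and control groups post-training".

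The same section sets one threshold for all of them: "All tests will be applied assuming a 95% confidence level", with P<0.05 as significant. The t tests are not made conditional on the interaction, and the paired tests are not labelled descriptive.

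The sample size section uses a two-sample t test on VO2peak after the intervention: difference 0.24 l/min, SDs 0.16 and 0.13, "α = 5% and power = 80"%, eight patients required and ten allocated per group.

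On other physiotherapy, which participants are asked to avoid, Participant withdrawal says: "This requirement will not be enforced in the period between the postintervention evaluation and the follow-up evaluation". Any use in that period is recorded.

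**The concern.** In every arm patients do 30 minutes of cycling per session plus breathing exercises, and there is no untrained arm. A pre-post change within one arm therefore mixes cycling, repeated testing and time with any effect of PNF. Testing each arm separately invites the conclusion that PNF works because its arm reached significance and the control arm did not. A difference in significance is not a significant difference.

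The other two procedures do compare arms, but neither is an ideal deciding test. The interaction over three visits has 2 degrees of freedom. It responds to any departure from parallel profiles, including one that arises only at the 30-day visit, when other physiotherapy is no longer discouraged. The independent t test targets the visit on which the trial was sized, but leaves out the pretraining value collected for every patient. With ten patients per arm that loss of precision matters.

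**Working it through.** **Inputs from the protocol article.** SDs 0.16 and 0.13; difference 0.24 l/min; alpha 5%; power 80%; 8 per arm required, 10 allocated. **Assumed, because the article gives neither:** the pre-post correlation rho (0.5 to 0.9) and the common pre-post gain (0 to 0.10 l/min). Equal SDs at both visits are also assumed.

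**1. The plan's own figure.** Pooled SD = sqrt((0.16² + 0.13²)/2) = 0.1458, so d = 0.24/0.1458 = 1.646. The exact two-sided t test has power 0.807 with 7 per arm and 0.864 with 8. With SD 0.16 in both arms, 8 per arm gives 0.797. Adding 20% loss: 8/0.8 = 10. The stated 8 and 10 are reproduced to within one patient and are not in question.

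**2. Paired tests when PNF adds nothing.** The SD of change is 0.1458 × sqrt(2(1 − rho)): 0.146, 0.113, 0.092 and 0.065 at rho 0.5, 0.7, 0.8 and 0.9. The standardised change is the gain divided by this SD. Let u be the chance that one arm is significant in the direction of improvement, and p the chance that it is significant in either direction (both from the noncentral t with n − 1 df). The arms are independent, so the chance that PNF is significant and control is not equals u(1 − p).

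| n per arm | rho | gain 0 | 0.02 | 0.04 | 0.06 | 0.08 | 0.10 l/min |
|---|---|---|---|---|---|---|---|
| 8 | 0.5 | 2.4% | 4.9% | 8.9% | 14.2% | 19.7% | 23.7% |
| 8 | 0.7 | 2.4% | 5.9% | 11.9% | 19.0% | 24.2% | 24.4% |
| 8 | 0.9 | 2.4% | 10.1% | 21.9% | 23.8% | 13.2% | 4.0% |
| 10 | 0.5 | 2.4% | 5.4% | 10.4% | 16.8% | 22.5% | 25.0% |
| 10 | 0.7 | 2.4% | 6.7% | 14.1% | 21.9% | 25.0% | 20.9% |
| 10 | 0.9 | 2.4% | 11.9% | 24.2% | 19.4% | 6.4% | 1.0% |

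The rate peaks at 25%, where each arm has about a 50% chance of significance. It falls again once both arms are nearly certain to be significant.

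**3. The two between-arm tests.** In simulation (20,000 runs per setting, rho 0.5 to 0.9, n = 8 and 10), type I error was 0.05 for the unadjusted post-training t test, for the pre-to-post change contrast (a single-contrast stand-in for the interaction) and for ANCOVA.

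**4. Precision of the post-training t test.** The ANCOVA variance is about (1 − rho²) times the unadjusted variance: 0.75, 0.51 and 0.36 at rho 0.5, 0.7 and 0.8. Estimating the slope multiplies this by about 1 + 1/(2n − 4). With 16 patients (1 + 1/12) the ratios become 0.81, 0.55 and 0.39; with 20 patients (1 + 1/16) they become 0.80, 0.54 and 0.38. Simulated power:

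| True difference, n per arm | Unadjusted | ANCOVA, rho 0.5 | ANCOVA, rho 0.7 | ANCOVA, rho 0.9 |
|---|---|---|---|---|
| 0.24 l/min, 8 | 0.86 | 0.92 | 0.98 | >0.99 |
| 0.12 l/min, 10 | about 0.42 | 0.50 | 0.66 | 0.97 |

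**5. Leaving the choice open.** With n = 10, rho 0.7 and no PNF effect, count a trial as favouring PNF if any of three routes does so: the paired pattern, the post-training t test or the change contrast. This happens in 6% to 26% of trials as the common gain runs from 0 to 1 baseline SD. Each between-arm test alone favours PNF in about 2.5%, so at the higher rates nearly all of the excess comes from the paired route.

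**The case against.** A reader might infer that the plan as a whole tests efficacy without a proper comparison and throws the baseline away. The text does not support that. The first procedure listed is a between-arm interaction that includes the pretraining visit; only the independent t test omits baseline.

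A reader might also infer that chance baseline imbalance makes the post-training t test produce false benefits. At 8 per arm the chance of a baseline difference above 0.5 SD is about 32% (26% at 10 per arm), but randomisation already allows for this in the standard error, and the test keeps its 5% error. It also matches the sample-size calculation. Its fault is lost precision. That loss is smaller if the comparator is a change-score contrast, where the ANCOVA variance ratio is (1 + rho)/2: 0.75, 0.85 and 0.90 at rho 0.5, 0.7 and 0.8.

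The 25% figure is the top of a curve over assumed inputs, and it applies only under a decision rule that the article never states. Both points stand, which is why the full range is shown. The article does nothing to rule that reading out, however: the paired tests share the significance threshold of the between-arm tests and have no stated role.

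Finally, a ranking among tests may sit in a full protocol or analysis plan that is not shown, so its absence here is not a fault by itself. What the article does fix is an inferential within-arm test in each arm and an unadjusted comparison at the key visit. The relaxed physiotherapy rule applies to all arms, and including the 30-day visit is a legitimate choice; it is simply not the contrast on which the trial was sized.

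**Conclusion.** The point holds in a limited form and should be fixed.

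- **Paired tests.** They cannot show what PNF adds. With no PNF effect and equal gains in both arms, significance in the PNF arm alone occurs in about 1% to 25% of trials per outcome and limb pair (2.4% with no gain). This rests on assumed gains of 0 to 0.10 l/min and correlations of 0.5 to 0.9, and does harm only if the paired results are taken as efficacy evidence.
- **Interaction.** It is a valid between-arm test that uses baseline, but its 2-df form does not isolate the post-training difference.
- **Post-training t test.** It is valid but inefficient. Baseline adjustment would leave roughly 0.75, 0.51 or 0.36 of its variance at assumed correlations of 0.5, 0.7 or 0.8, slightly more after the small-sample cost.

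The sample size is not affected.

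**What to change.** In Statistical analyses, for each limb pair:

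- Name as the decisive analysis the between-arm difference at post-training adjusted for the pretraining value, with a 95% confidence interval. Use ANCOVA, or the post-training contrast of a mixed model that includes baseline. It replaces the unadjusted independent t test.
- Make the 30-day between-arm contrast secondary.
- Report within-arm changes descriptively, and state that their P values are not evidence of a PNF effect.

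This costs a change of wording and about one degree of freedom. It needs no new data or patients, and the article reports recruitment as ongoing, so the change can be made before analysis.
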